### Interim analyses {21b}

Not applicable in our protocol. Interim analysis and stopping guideline were not planned in our study because intervention and follow-up time is not long.

### Methods for additional analyses (e.g. subgroup analyses) {20b}

In additional analyses, the dosage of NCVs, genders, ages, and any experience of receiving AA therapy will be determined for each treatment arm.

### Methods in analysis to handle protocol non-adherence and any statistical methods to handle missing data {20c}

Clinical outcomes will be analysed in both intention-to-treat (ITT) and per-protocol (PP) participants, and missing values will be imputed by the last-observation-carried forward method. Results of participants who received AA (auricular acupressure), SAA (sham auricular acupressure) or WL (wait-list) observation, and with baseline details recorded will be processed with ITT analyses, while those who complete all the 14-day evaluation and with the interventions applied correctly will be analysed with PP sets.

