## Introduction

### Background and rationale {6a}

As of October 5, 2021, a total of 234 million people were confirmed infected with SARS-CoV-2, including 4.8 million deaths worldwide [1]. Developing immunity through COVID-19 vaccination provides a reduced risk of being infected and helps to fight the virus if exposed, which can save uncounted lives and give us a pathway out of the global disaster [2, 3]. Researches showed that novel coronavirus-19 vaccines (NCV) were of considerable efficacy, and improvement on efficacy, especially long-term protection, and exploration of new species of vaccines are being conducted [4–8]. Some new variants of COVID-19 have been emerging, which may exacerbate COVID-19 symptoms, while researches reveal that many still with good immunogenicity [9, 10]. However, some studies show concern on prevention efficacy in the situation [11, 12]. For this, some researchers argue for strengthening injection of current NCV; simultaneously, new NCVs are being developed by countries [13, 14]. According to the WHO, till October 5, 2021, 124 of NCV products are in clinical development, and 194 are in pre-clinical development worldwide, with the top three types of NCVs listed as protein subunit (43, 35%), viral vector (non-replicating, 18, 15%), and DNA (12, 10%) [15].

Clinical experiments observed some adverse events following immunization (AEFI) in potential association with injection of NCVs, though most of them disappeared after several or a dozen days without special medical intervention. Among them, most frequent events were localized reactions (such as pain, sore, swelling, and itching), followed by fatigue, fever (some with chills), headache, myalgia, dizziness, and nausea (some with vomiting) [4–6, 16–19]. Mechanically, most AEFI are induced by hypersensitivity of organs or immune response to vaccine, which is more obvious in strengthening injection of NCV, especially [20, 21].

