### Eligibility criteria {10}

#### Inclusion criteria

Vaccinators will be screened strictly for meeting the criteria of the NCV injection shortly before the injection (during registration) [31]. Patients will be included if they meet all the following criteria:
Conforming to the conditions of the injection without contraindication, and completing the NCV injection within 24 h before screeningNo headache, muscle or joint pain, fatigue, diarrhoea, nausea, or vomiting experienced (no more than 4 scores, VAS) within 3 days before the injection, and no diseases (diagnosed) presenting the symptoms aboveNo redness, swelling, injury, or infection on the skin or soft tissue of bilateral earsNo history of alcohol and adhesive tape contact allergyAble to complete the follow-up questionnaires independently online or by phoneAgree to participate and sign the informed consent, and abide by precautions after the injection and requirements of AA therapy

In addition, it should be pointed out that due to the emergency of NCV injection and the good safety of AA therapy, we do not restrict ages and genders among participants. We will conduct sub-groups for different ages for comparison.

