### Outcomes {12}

All outcomes will be accessed and evaluated from the participants online or by phone in 1, 3, 5, 7, and 14 days after NCV injection, which they thought might be related to the injection. Primary outcomes are percentages of participants who reported any AEFI and who reported local pain at injection site, with their severity evaluated by visual analogue scale (VAS) scores of 0–10. Secondary outcomes include percentages of participants who reported headache, muscle and (or) joint pain, fatigue, nausea, vomiting, and diarrhoea, together with other AEFI reported by participants but not listed above, and with their severity evaluated by the VAS scores, similarly.

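### Last observation carried forward is the only missing-data method for symptoms the protocol expects to resolve, so it can distort later-visit results and, if loss differs by arm, the comparisons

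*Protocol article*

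**What the plan says.** Section {20c} of the protocol article fixes one rule for the clinical outcomes: "missing values will be imputed by the last-observation-carried forward method". It names no other method and no sensitivity analysis for missing data. The intention-to-treat (ITT) set is those who received their allocation "and with baseline details recorded will be processed with ITT analyses", so no post-baseline contact is required. The per-protocol (PP) set is narrower: "while those who complete all the 14-day evaluation and with the interventions applied correctly will be analysed with PP sets".

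Outcomes {12} are collected "online or by phone in 1, 3, 5, 7, and 14 days after NCV injection". On the primary outcomes it says: "Primary outcomes are percentages of participants who reported any AEFI and who reported local pain at injection site", with severity on a 0–10 VAS. It does not say whether a percentage is per visit or cumulative over the 14 days.

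The background {6a} describes the natural course of these events: "though most of them disappeared after several or a dozen days without special medical intervention".

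**The concern.** Carrying the last value forward is harmless only if the outcome would have stayed where it was after contact was lost. The protocol says the opposite: most AEFI go away untreated within several days to about a dozen. The five follow-up days lie in that window.

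Three consequences follow. First, a participant last heard from with pain on day 1 is recorded as in pain on days 3, 5, 7 and 14. One with no follow-up contact stays in the ITT set and is given the baseline value. Second, imputed values are analysed as if they had been observed, so the confidence intervals ignore the uncertainty about them. Third, if arms lose different numbers of participants, or lose them at different times, the carried values enter the arms unequally and can create or mask a difference. Both primary outcomes and their VAS scores are exposed. The comparison most open to this is auricular acupressure (AA) against wait-list (WL), because only the WL participants know their allocation and they receive no tapes.

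**Working it through.** The protocol has no dropout rate, event rate or power figure to reproduce (Sample size {14} says none was calculated). The following is an illustration on assumed rates.

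**Inputs.** From the protocol: at least 360 participants randomised 1:1:1, so 120 per arm; visits on days 1, 3, 5, 7 and 14; two-sided 5% level. Assumed: pain prevalence of 40%, 20%, 10% and 4% on days 1, 3, 5 and 7, identical in every arm (no treatment effect); loss unrelated to symptoms; percentages read per visit.

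**Formula.** If a share d of an arm is lost before day 7, and pain prevalence at their last contact averages q, the carried-forward day-7 percentage is (1 − d) × 4% + d × q.

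**All loss after day 1 (q = 40%).**
- d = 15%: 0.85 × 4% + 0.15 × 40% = 3.4% + 6.0% = 9.4%.
- d = 5%: 0.95 × 4% + 0.05 × 40% = 3.8% + 2.0% = 5.8%.
- False difference: 3.6 points.

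**Last contact spread evenly over days 1, 3 and 5 (q = (40 + 20 + 10)/3 = 23.3%).**
- d = 15%: 3.4% + 3.5% = 6.9%.
- d = 5%: 3.8% + 1.2% = 5.0%.
- False difference: about 1.9 points.

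**Equal loss, same timing.** d = 10% in both arms, all after day 1: 3.6% + 4.0% = 7.6% in each. The level is nearly doubled, but there is no false difference.

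**Equal loss, different timing.** d = 15% in both arms, one losing all after day 1 and the other evenly: 9.4% versus 6.9%, a false difference of 2.5 points.

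**False-positive rates** at day 7, exact enumeration with 120 per arm:

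| Loss | Fisher | Uncorrected chi-square |
|---|---|---|
| 10% vs 10%, after day 1 | 2.6% | 5.4% |
| 15% vs 5%, after day 1 | 11.8% | 19.0% |
| 15% vs 5%, spread | 5.1% | 9.8% |

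The Statistical methods section {20a} allows either test as appropriate. Expected counts here are about 7 to 9 events per arm. Fisher's null rate is itself well below 5%, so each column should be judged against its own equal-loss row.

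**A true effect with equal loss.** Assume day-1 and day-14 prevalences of 40% and 2% in WL, half that in AA, and 10% loss after day 1 in both. Day 14 reads 0.9 × 2% + 0.1 × 40% = 5.8% in WL and 0.9 × 1% + 0.1 × 20% = 2.9% in AA. The difference is 2.9 points against a true 1.0. So equal loss protects the test under no effect, but not the size of a real per-visit difference.

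**Cumulative reading.** If the percentage means ever reported by day 14, a participant already positive stays positive and carrying that forward changes nothing. The remaining error is a participant lost before onset, who is counted as event-free. VAS scores by visit are affected under either reading.

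**The case against.** The strongest reply is that the trial is explorative, follow-up is only 14 days, and the protocol tries to limit missing data. The withdrawal section asks that withdrawn participants be followed where possible for the ITT analysis, and section {18b} encourages those who stop or deviate to keep reporting. A PP analysis of completers is also planned. If loss is small and similar across arms, the comparison under no effect is barely touched. That much stands. It limits how much is imputed, but does not make the rule suitable for what is. The PP set needs little imputation, but it is selected after randomisation and cannot stand in for the ITT result.

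Four stronger readings are tempting, and the documents do not support them.
- *Dropout rather than treatment determines the later percentages.* That needs heavy early loss or marked imbalance between arms, and no dropout rate is given.
- *Retention incentives favour the AA and sham arms.* Sections {11c} and {18b} promise two free sessions on completion and do not exclude WL. WL also has no daily pressing to do, so it could lose fewer participants. The case for unequal loss rests on unblinding and lack of tapes, and its direction is not known. The blinded AA and sham arms get like procedures, so there is less reason to expect imbalance between them.
- *Anyone with baseline data only is scored as pain-free.* The baseline assessment follows the injection. The entry limit is "fatigue, diarrhoea, nausea, or vomiting experienced (no more than 4 scores, VAS) within 3 days before the injection", which tolerates mild symptoms, and the criterion does not list injection-site pain. The baseline pain percentage is therefore unknown, and no day-1 bias can be calculated.
- *A participant withdrawn for a serious adverse event keeps the value before it.* Continued follow-up is requested, so this is not automatic. Counting every such event as an AEFI would also conflict with section {12}, which limits outcomes to events the participant thought might be related to the injection.

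**Conclusion.** The point holds in a limited form. The stated rule conflicts with the protocol's own account of the symptom course. It can distort later per-visit percentages and VAS scores, and it leaves the uncertainty of imputed values out of the intervals. It can bias between-arm comparisons when the amount or timing of loss differs, most plausibly those involving WL.

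The size cannot be established from the protocol. On the assumed rates, 15% versus 5% loss produces a false day-7 difference of 1.9 to 3.6 points depending on when loss occurs, and none if amount and timing are equal. These figures assume per-visit percentages and loss unrelated to symptoms. On a cumulative reading, the harm to the percentages is mainly missed later onset.

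**What to change.** In section {20c}, replace last observation carried forward in the ITT analysis with multiple imputation, or a repeated-measures model, under missing-at-random. Use the observed days, arm, centre and baseline. Keep the planned comparisons of percentages with their 95% confidence intervals. State whether each primary percentage is per visit or cumulative. Add one missing-not-at-random sensitivity analysis (a delta shift or tipping point) for loss related to symptoms.

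The cost is revised analysis wording and modest programming. No new data or participants are needed. Intervals may be somewhat wider because they will carry the imputation uncertainty.

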#### Withdraw from the trial

Participants will be allowed or asked to drop out from the trial if they:
Are lost to follow-upBecome pregnantDevelop serious adverse event (SAE)

Participants can withdraw from this clinical trial at any time. The date and reason for withdrawal should be stated. If possible, all subjects withdrawing from the study should continue to be followed up regularly on a measurement schedule with a final assessment for intention-to-treat analysis.

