**Fig. 3 Fig3:**
[figure not shown]
The Semen Vaccariae tapes in our study

Surface of the auricular acupoints, marked on stick figures with two protocols associated with the sequence numbers for AA and SAA, was cleaned and dried with disinfection swabs, and Semen Vaccariae tapes were pasted in the acupoints by the acupuncturists and pressed with fingers to achieve sensation of soreness or distention.

In addition, the participants in AA and SAA groups were informed to press the tapes by themselves for 1 min vertically and appropriately to achieve the sensation, with a duration of 4 to 5 times a day and 5 days in total. The content above was written in Attention After AA Therapy, which were distributed to the participants with the individual sequence number recorded.

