## Assignment of interventions: allocation

### Sequence generation {16a}

After confirmation for eligibility and collection of written informed consents, participants will be randomized through a random allocation software (The Hefei Big Orange Software Technology Co., Ltd, V 2.1.8), and be allocated to the AA, SAA, and WL groups in a 1:1:1 ratio with stratifying by centres.

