## Assignment of interventions: blinding

### Who will be blinded {17a}

The participants in the AA group and SAA group, outcome assessors, and statisticians will be blinded, while participants in the WL group and the acupuncturists will not.

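### The set labelled intention-to-treat is a modified ITT set conditioned on receiving the allocation and on recorded baseline, and it can lose participants from AA and SAA but hardly from WL

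*Protocol article*

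**What the plan says.** Section {20c} is the only place where the protocol article defines its analysis sets. The ITT set is restricted to participants who received AA, SAA "or WL (wait-list) observation, and with baseline details recorded will be processed with ITT analyses". The per-protocol (PP) set is defined by "those who complete all the 14-day evaluation and with the interventions applied correctly will be analysed with PP sets". Missing values are to be filled by last observation carried forward (LOCF).

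Four other sections bear on the definition:

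- Sequence generation {16a}: "After confirmation for eligibility and collection of written informed consents, participants will be randomized". Eligibility and consent are the only preconditions named.
- Intervention description {11a}: acupuncturists paste the tapes in AA and SAA, after which "the participants in AA and SAA groups were informed to press the tapes by themselves for 1 min vertically". WL has no procedure.
- Who will be blinded {17a}: participants in AA and SAA, outcome assessors and statisticians are blinded, but "participants in the WL group and the acupuncturists will not".
- Withdraw from the trial: where possible, "all subjects withdrawing from the study should continue to be followed up regularly on a measurement schedule with a final assessment for intention-to-treat analysis".

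**The concern.** An intention-to-treat analysis includes everyone randomised, in the arm to which they were randomised. That is what protects the comparison from selection after allocation. Here membership depends on receipt, which comes after allocation, and on a baseline record that is not stated to come before it. The word received also leaves room for analysis by treatment received, and no sentence rules that out.

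The receipt condition does not act alike in all arms. Someone assigned to AA or SAA who declines the tapes or leaves before taping drops out of the set. Someone assigned to WL has almost nothing to fail to receive. If those lost differ in their risk of an AEFI, the comparisons with WL are shifted, and the protocol describes no other analysis of all randomised participants that would show it.

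**Working it through.** **1. The text, set side by side.** There is no calculated figure in the plan to reproduce. The sample size of at least 360 has no stated event rate, effect or dropout, and 360 / 3 = 120 per arm is the only arithmetic available.

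| Condition for the ITT set | When it is settled | Who can fail it |
|---|---|---|
| Received AA or SAA | After randomisation, at taping | Anyone in AA or SAA who is not taped |
| Received WL observation | After randomisation | Hardly anyone |
| Baseline details recorded | Not stated; {16a} names only eligibility and consent | Any arm |

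The withdrawal section does not repair this. It asks that people who withdraw be followed "with a final assessment for intention-to-treat analysis". Yet a person who withdraws between randomisation and taping is still shut out of that analysis by {20c}.

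**2. How large could the effect be?** The protocol gives no exclusion rate and no event rates, so everything here except the 120 per arm and the two-sided 5% level is an assumption. Suppose there is no true effect and a common AEFI rate *p*. A fraction *f* is lost from AA only, and those lost have rate *q*. The AA rate among those kept is

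(p − f·q) / (1 − f), and the shift is that value minus p.

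Worked case, p = 0.30, f = 0.05, q = 0.60: (0.30 − 0.05 × 0.60) / 0.95 = 0.27 / 0.95 = 0.284, a shift of −1.6 points. With 114 in AA and 120 in WL, the standard error is √(0.284 × 0.716 / 114 + 0.30 × 0.70 / 120) = 0.0594. The type I error at the two-sided 5% level is then 0.058 (normal approximation).

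| f lost from AA only | q = 0.60 (twice p) | q = 0.30 (same as p) | q = 0.15 (half p) |
|---|---|---|---|
| 2% | −0.6 points; type I error 0.051 | 0; 0.050 | +0.3 points |
| 5% | −1.6 points; 0.058 | 0; 0.050 | +0.8 points |
| 10% | −3.3 points; 0.086 | 0; 0.050 | +1.7 points |

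The last column uses the same formula: (0.30 − 0.02 × 0.15) / 0.98 = 0.303, (0.30 − 0.05 × 0.15) / 0.95 = 0.308 and (0.30 − 0.10 × 0.15) / 0.90 = 0.317.

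With q = 2p at other base rates:

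- p = 0.20: −1.1 points (type I error 0.055) at 5% lost and −2.2 points (0.071) at 10%.
- p = 0.50: −2.6 points (0.069) at 5% lost and −5.6 points (0.134) at 10%.

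For scale, with 120 per arm and a rate of 30% the standard error of a difference is √(2 × 0.30 × 0.70 / 120) = 0.059, about 6 points.

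**3. What this shows.** The shift is zero when those lost resemble the rest, changes sign with their risk, and is small against sampling error when few are lost.

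**The case against.** The best defence is that the receipt condition will seldom exclude anyone. Recruitment takes place during on-site observation after the injection, participants agree in writing to the requirements of the therapy, and the Abstract says that the interventions are performed immediately. Eligibility already calls for symptom scores over the preceding 3 days, so much baseline information must exist before randomisation. The body of Table 2 was not available for this review and may place baseline before allocation. The trial is also declared explorative. All of this limits the likely size. None of it changes the definition, which is written out in full and so is not a detail left to a later document.

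A reader might infer more than the text supports:

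- *That the PP definition is itself an error.* A PP set is never expected to preserve randomisation, and the rule is worded identically for all arms. Its correct-application condition can in practice exclude people only in AA and SAA. That is a reason to keep PP supportive, not a separate fault.
- *That AA vs SAA is equally compromised.* Both arms have five bilateral points, taping, self-pressing and blinded participants. The acupuncturists know the allocation, but the document points to no mechanism for unequal losses between these two arms.
- *That withdrawal for a serious adverse event removes people only from the taped arms.* That withdrawal criterion applies to every arm.
- *That ITT and PP are given equal standing.* The article says only that both will be done, and the order of priority may be fixed in an analysis plan that is not shown.

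**Conclusion.** The concern holds as a wrongly stated definition. The set called ITT is a modified ITT set conditioned on an event after randomisation, and the text does not commit to analysis as randomised. The exposure lies mainly in AA vs WL and SAA vs WL.

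It would be tempting to say that the definition favours AA by a given number of points. The document does not support that. The share lost, their event rate and the direction are all unknown, and the figures above only show how the shift depends on them. If few are lost before taping, as the on-site procedure suggests, the shift is probably small. The case for correction is that the stated rule gives up the protection of randomisation when it could be kept at little cost.

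**What to change.** Replace the ITT sentence in {20c} with wording to this effect: the ITT set is all randomised participants, analysed in the arm to which they were assigned, regardless of the intervention received or whether baseline details were recorded.

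Then:

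- State how participants with no observation after randomisation are handled, because LOCF has nothing to carry forward for them.
- If the present set is kept as well, call it modified ITT and report by arm how many it excludes and why.
- Base the main conclusion on ITT, with PP as supportive.

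The randomisation records already identify everyone, so no new data collection is needed. The cost is revised wording, one missing-data rule, and a few participants with missing outcomes in the main analysis.

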### Plans to give access to the full protocol, participant-level data, and statistical code {31c}

Results of this study will be disseminated through publication (with no restriction) and academic conferences. The datasets used and analysed during the current study are available from the corresponding author on reasonable request.

## Oversight and monitoring

### Composition of the coordinating centre and trial steering committee {5d}

Coordinating centre, steering committee, endpoint adjudication committee, and data management team were gathered for our study. Coordinating centre and steering committee are responsible for general monitoring and providing organizational support. They also involved in study design, interpretation of data, writing of the report, and the decision to submit the report for publication. Endpoint adjudication committee and data management team are responsible for providing day to day support for the trial, including participant evaluation, collection, management, withdraws, analysis, and follow-up.

